## Abstract

**Introduction:**

*Streptococcus pneumoniae* (the pneumococcus) is commonly carried as a commensal bacterium in the nasopharynx but can cause life-threatening disease. Transmission occurs by human respiratory droplets and interruption of this process provides herd immunity. A 2017 WHO Consultation on Optimisation of pneumococcal conjugate vaccines (PCV) Impact highlighted a substantial research gap in investigating why the impact of PCV vaccines in low-income countries has been lower than expected. Malawi introduced the 13-valent PCV (PCV13) into the national Expanded Programme of Immunisations in 2011, using a 3+0 (3 primary +0 booster doses) schedule. With evidence of greater impact of a 2+1 (2 primary +1 booster dose) schedule in other settings, including South Africa, Malawi’s National Immunisations Technical Advisory Group is seeking evidence of adequate superiority of a 2+1 schedule to inform vaccine policy.

**Methods:**

A pragmatic health centre-based evaluation comparing impact of a PCV13 schedule change from 3+0 to 2+1 in Blantyre district, Malawi. Twenty government health centres will be randomly selected, with ten implementing a 2+1 and 10 to continue with the 3+0 schedule. Health centres implementing 3+0 will serve as the direct comparator in evaluating 2+1 providing superior direct and indirect protection against pneumococcal carriage. Pneumococcal carriage surveys will evaluate carriage prevalence among children 15–24 months, randomised at household level, and schoolgoers 5–10 years of age, randomly selected from school registers. Carriage surveys will be conducted 18 and 33 months following 2+1 implementation.

**Analysis:**

The primary endpoint is powered to detect an effect size of 50% reduction in vaccine serotype (VT) carriage among vaccinated children 15–24 months old, expecting a 14% and 7% VT carriage prevalence in the 3+0 and 2+1 arms, respectively.

**Ethics and dissemination:**

The study has been approved by the Malawi College of Medicine Research Ethics Committee (COMREC; Ref: P05.19.2680), the University College London Research Ethics Committee (Ref: 8603.002) and the University of Liverpool Research Ethics Committee (Ref: 5439). The results from this study will be actively disseminated through manuscript publications and conference presentations.

**Trial registration number:**

NCT04078997.

Strengths and limitations of this studyThe study is supported by more than 20 years of routine pneumococcal surveillance.The study design is both pragmatic and robust, offering a methodology that is relevant to diverse settings in the region.By engaging community, institutional and government partners, we have optimised its relevance and increased the likelihood of community uptake.Limitations to this study include a risk of contamination between clusters (*ie,* children receiving a 2+1 vaccine schedule who reside in or relocate to a cluster implementing the 3+0 vaccine schedule or vice-versa).

## Introduction

*Streptococcus pneumoniae*, the pneumococcus, is commonly carried as a commensal bacterium in the nasopharynx but can cause life-threatening disease. Infections due to the pneumococcus are estimated to be responsible for approximately 300 000 deaths worldwide, with one-third of these occurring among children under 5 years of age and with the greatest burden in low- and middle-income country settings.^1 2^

*S. pneumoniae* has almost 100 serotypes, with nasopharyngeal (NP) carriage as a prerequisite for the development of disease but also a key process for developing natural immunity.^3^ Transmission occurs largely *via* human respiratory air droplets. With serotype-specific differences, carriage duration decreases with age, lasting from 2 weeks in adults up to 4 months among children.^4 5^ Pneumococcal carriage prevalence is age-dependent, peaking among children <5 years. Pneumococcal carriage prevalence reported in sub-Sahara Africa are among the highest described; up to 28% among adults and in excess of 80% in children <5 years old, resulting in high transmission rates.^6–14^

In HICs, routine administration of pneumococcal conjugate vaccines (PCV) through the infant immunisation schedule has contributed to a rapid decline of vaccine serotype invasive pneumococcal disease (VT-IPD) in both vaccinated and unvaccinated populations.^15–23^ PCVs protect the vaccinated individual (direct protection) against pneumococcal disease and carriage. The resulting reduction in carriage also interrupts transmission from the vaccinated individual to the unvaccinated population (indirect protection). The resulting herd immunity effect has been a major contributor to the success of vaccination programmes.^24–26^ The added cost-effectiveness and vaccine impact gained through indirect protection have been key drivers of vaccination policy in these settings.^27 28^ PCV impact on pneumococcal carriage continues to be considered a viable endpoint in vaccine licensure evaluations.^29^

Studies undertaken prior to PCV introduction in The Gambia, Kenya, Mozambique, Malawi and South Africa reported VT carriage prevalence ranging from 28% to nearly 50% among children <5 years old.^30–33^ While PCV introduction in African countries has resulted in substantial direct effects in reducing risk of VT-IPD,^34^ pneumonia and all-cause mortality^35^ among vaccinated children,^10 11 36^ the impact of PCV on VT carriage has been markedly less than that observed in HICs. Although Kenya,^12^ the Gambia,^13^ Mozambique^14^ and South Africa^31^ have reported VT carriage reductions, prevalence remains higher than expected, and serotype replacement (ie, rise in non-VT carriage prevalence associated with decrease in VT carriage) is increasing.^6 37^ As the impact of PCV on carriage is considered an indicator of vaccine impact,^29^ it remains uncertain whether PCV introduction in sub-Sahara Africa will achieve the sustained direct or indirect protection necessary to reduce pneumococcal carriage to levels sufficient to interrupt transmission and disease.^38^

Currently, WHO recommends the implementation of the PCV vaccine using either a 3+0 schedule (three primary doses, most commonly at 6, 10, and 14 weeks of age) or a 2+1 schedule (two primary infancy doses at 6 and 14 weeks of age and one booster at 9 months of age or after the first year of life). The WHO further recommends that the decision on which schedule to use be based on the epidemiology of disease in the local setting.^39^ While both schedules have been shown to be effective in reducing VT disease and VT carriage, there have been no direct comparisons of vaccine impact on carriage in a high burden setting.^40^

A 2017 WHO Technical Expert Consultation on Optimisation of PCV Impact highlighted a substantial research gap in investigating why the impact of PCV vaccines in low-income countries has been less than expected, underlining the need to define an optimal PCV vaccination schedule that will maximise their benefit in such settings.^41^ The PCV Review of Impact Evidence, commissioned to supplement the WHO Expert Consultation, is a systematic review of available evidence on PCV effectiveness and impact on NP carriage, disease and mortality, as well as on PCV immune response. The review included evidence from research studies published between January 2010 and December 2016 recorded in 14 databases. Those attending the 2017 WHO Technical Expert Consultation gave head-to-head studies of 2+1 vs 3+0 vaccine schedules the greatest research priority.^42^ Countries with a high pneumococcal disease and carriage burden, such as Malawi, could implement a 2+1 schedule quickly, with limited logistical or financial demands, providing a booster dose at the time of the first measles vaccine at 9 months of age.

Malawi introduced the 13-valent PCV (PCV13) into the national Expanded Programme of Immunisations (EPI) in November 2011, using a 3+0 schedule (6, 10 and 14 weeks of age), with a three-dose catch-up vaccination campaign among all infants <1 year of age. This introduction has been highly successful, with field studies showing an EPI vaccine coverage exceeding 90%.^43 44^ Similar to other settings, vaccine introduction resulted in a~70% reduction in IPD among PCV-vaccinated children^34^ and an estimated 35% fall in all-cause mortality.^35^ However, high levels of residual VT carriage persist in Malawi among vaccinated children up to 8 years after the introduction of the vaccine.^45^ As presented by Lourenço *et al*^46^ a high force of infection in settings such as Malawi contribute significantly to a 3+0 schedule achieving only a short duration of VT carriage control in infants. Though a 2+1 schedule, as implemented in South Africa, may improve colonisation control, this remains unproven in other African settings such as Malawi.

In this context, the Malawi Ministry of Health (MoH) and the National Immunisations Technical Advisory Group are now seeking evidence of adequate superiority of a 2+1 vaccine schedule to inform a change to Malawi’s current EPI schedule. To this aim, a pragmatic health centre-based evaluation comparing the current 3+0 schedule to a 2+1 schedule will be implemented in Blantyre District, southern Malawi. Two pneumococcal carriage surveys, conducted 18 and 33 months following the implementation of the 2+1 schedule, will have the objective of comparing the effect of the two schedules against carriage reduction among otherwise-healthy children and evaluate their potential to enhance herd immunity.

## Methods and analysis

### Study design

The study is a pragmatic health centre-based randomised evaluation of the direct effect of a 2+1 PCV13 vaccine schedule on pneumococcal carriage in vaccinated infants and the indirect effect on non-vaccine eligible children and high-risk adults.

### Study setting

The study will be conducted in Blantyre district, southern Malawi. The District is 240 km^2^. Healthcare is delivered through a network of private and government hospitals and 28 government primary health centres, where EPI vaccinations are administered. Queen Elizabeth Central Hospital (QECH) is the government referral hospital providing free medical care to the 1.3 million urban, periurban and rural residents of Blantyre District. Children <5 years account for 16% of the total population.^47^ Health centres cover a fixed geographic area (here referred to as ‘clusters’), and study sampling will be undertaken within these clusters (figure 1).

**Figure 1 F1:**
[figure not shown]
Map of Blantyre district with borders of health centre catchment areas. Red crosses (+) indicate location of health centres offering EPI vaccination. Areas shaded in green are non-inhabited (incl. mountains, industrial zones and other regions administratively declared not for habitation). EPI, Expanded Programme of Immunisations.

### Study questions

We will investigate whether a 2+1 PCV13 vaccination schedule (two primary doses at 6 and 14 weeks of age +1 booster dose at 9 months of age), compared with the current 3+0 schedule (three primary doses at 6, 10 and 14 weeks of age with no booster), is superior in reducing VT carriage prevalence among vaccinated children and, consequently, creating a superior herd effect among older children and HIV-infected adults. To assess the effect of a district-wide change from 3+0 to 2+1, this study will address two specific research questions: First, will a 2+1 schedule provide enduring vaccine-induced protection against pneumococcal VT carriage into the second year of life? Second, will the 2+1 vaccine schedule generate stronger herd protection and result in decreased VT carriage in older children and unvaccinated high-risk adults in the general population?

### Primary objective

The primary objective of the study is to evaluate the direct effect of a 2+1 PCV13 vaccination schedule on VT pneumococcal carriage among children aged 15–24 months, 3 years after introducing the 2+1 schedule. This objective will answer the question of whether the 2+1 schedule induces a more enduring direct protection against pneumococcal VT carriage into the second year of life, compared with that observed with a 3+0 schedule.

### Secondary objectives

The secondary objectives of the study are to evaluate, 3 years after introducing the 2+1 schedule, (1) the indirect effect of a 2+1 schedule on VT pneumococcal carriage among children aged 5–10 years (PCV age-ineligible at time of implementing the 2+1 schedule); (2) the indirect effect of a 2+1 vaccination schedule on VT pneumococcal carriage among HIV-infected adults 18–40 years old and on antiretroviral therapy (ART).

To address these questions, the Malawi MoH and Blantyre District Health Office (DHO) will randomly select 10 health centres (among a total 28 in Blantyre District) in which the routine PCV13 schedule will be switched to a 2+1 schedule. An additional 10 health centres will be randomly selected to continue with the current 3+0 schedule but will serve as the direct comparator in evaluating the effectiveness of the 2+1 schedule.

### A pragmatic study design

This switch to a 2+1 schedule is an initiative led by the MoH and will be implemented within the scope of the routine EPI programme, subject to EPI standard procedures for delivery, monitoring and performance assessment. Implementation of all vaccination activities will be implemented, as per routine practices, by MoH EPI vaccinators through the routine EPI programme. The MoH will monitor completeness of dosing following standard reporting practices within the scope of the EPI. Routine study activities throughout the duration of the 3-year study period will include research nurses providing support and guidance to the EPI vaccination teams through weekly site visits. In addition, research enumerators will monitor patient-retained health passports of a representative sample population of vaccinees to confirm they are receiving the proper vaccine schedule (2+1 or 3+0) assigned to the catchment population of their respective health centre.

The pragmatic design of this study has been assessed through the tool The PRagmatic-Explanatory Continuum Indicator Summary 2 (PRECIS-2).^48^ This tool was developed to help trialists make design decisions consistent with the intended purpose of their trial. To facilitate domain discussion and consensus, PRECIS-2 assesses the pragmatic design through nine domains—eligibility criteria, recruitment, setting, organisation, flexibility (delivery), flexibility (adherence), follow-up, primary outcome and primary analysis—scored from 1 (very explanatory) to 5 (very pragmatic). The report from this tool is in the format of a wheel (figure 2). Results (mean score: 4.4 and range: 3–5) supports that this is largely a pragmatic randomised study undertaken in the ‘real world’ and with usual care and is intended to help support a decision on whether to deliver an intervention.

**Figure 2 F2:**
[figure not shown]
The PRagmatic-Explanatory Continuum Indicator Summary 2 wheel with study-specific scores.

### 3+1 schedule during early period of initiation

To ensure the 2+1 schedule is implemented efficiently, and to limit the risk of confusion during the transition to the 2+1 schedule (including not deferring PCV13 vaccination to a later visit), a 3+1 schedule will be implemented during the first several months at health centres implementing the 2+1 schedule. At these health centres, children who have received either their 10 weeks or 14 weeks PCV13 dose before 2+1 implementation will receive a dose at their 14 weeks (third dose PCV13) and their 40 weeks (fourth dose PCV13). Approximately 6 months after 2+1 implementation, all first-contact vaccine visits (post 2+1 implementation) will be for the scheduled visit at 6 weeks of age and the 3+1 schedule will no longer be required.

### Carriage surveys

The study will include two cross-sectional carriage surveys, implemented 18 and 33 months after the switch to 2+1. Carriage surveys will be conducted using a well-established methodology implemented extensively in the setting,^45 46^ allowing comparability of study results to previous carriage surveys conducted in the area. The sampling frame is illustrated in figure 3.

**Figure 3 F3:**
[figure not shown]
Carriage surveillance sampling frame black dashed vertical line separates primary (left of dashed line) from secondary study objectives. ART, antiretroviral; M, months; PCV, pneumococcal conjugate; QECH, Queen Elizabeth Central Hospital.

Sampling will include:

Children 15–24 months of age, PCV13-vaccinated (confirmed by reviewing patient-retained health passports) with either the 2+1 or the 3+0 schedule. Evaluation within this age group will allow us to evaluate for our primary objective, evaluating the direct effect of vaccination on carriage. Within each of the catchment areas of the 20 participating health centres, we will conduct a random walk method to systematically identify households with eligible children. A ‘egg and yolk’ strategy will be applied, defining two geographic sampling perimeters around each health centre. Sampling will prioritise those living within the geographic perimeter closest to the health centre. In the event that recruitment targets are not met, sampling will move into the second geographic perimeter. This strategy will maximise the likelihood of recruiting children who have received their vaccines at the selected health centre, minimising recruitment from buffer zonal borders and therefore minimising risk of contamination (ie, recruitment of children receiving a PCV13 vaccine schedule different than the schedule assigned to the child’s local health centre).Children 5–10 years of age, PCV13-vaccinated with the 3+0 schedule. These children, having received PCV13 at infancy, will be recruited from government schools. Evaluation within this age group will allow us to evaluate for a secondary objective, evaluating the indirect effect of a 2+1 schedule on VT pneumococcal carriage among children aged 5–10 years, the majority of whom received PCV13 infancy EPI vaccination using a 3+0 schedule. Six schools will be selected, three located centrally in each of the 3+0 clusters and the 2+1 clusters. Children will be chosen at random from school registers. This component will allow the evaluation of indirect effects of the 2+1 compared with 3+0 schedule among children with waning vaccine-induced immunity.Adults 18–40 years of age, HIV-infected on ART and PCV13-unvaccinated. Evaluation within group will allow us to achieve the secondary objective of evaluating the indirect effect of a 2+1 schedule on VT pneumococcal carriage among HIV-infected adults (18–40 years) on ART, a population at high risk of pneumococcal disease. Participants will be recruited from the QECH, Lighthouse ART Clinic in Blantyre.

### Safety

To assess the differential effects of 3 vs 2 primary vaccine doses in the first year of life, an additional carriage survey will be implemented at health centres approximately 9 months after 2+1 implementation. A convenience sample of children aged 9 months will be recruited at health centres providing either the 2+1 or 3+0 schedule. This will allow an evaluation of carriage prevalence among children receiving 3 (according to the 3+0 schedule) vs 2 (according to the 2+1 schedule and presenting for their booster dose) primary doses. Additionally, this additional carriage survey will contribute to evaluating the coverage of the 2+1 vaccination schedule and the proportion of children receiving all three PCV13 doses at health centres providing the 2+1 schedule.

### Inclusion and exclusion criteria

Inclusion criteria for all individuals recruited includes permanent resident in Blantyre District. Among children 15–24 months of age (assigned to either 2+1 or 3+0 schedule), inclusion criteria additionally include: aged between 15 and 24 months, parent/legal guardian providing written informed consent, evidence (recorded in health passport) of having received a full schedule of PCV13. Among children 5–10 years of age, inclusion criteria include: aged between 5–10 years, parent/legal guardian providing written informed consent, providing written informed assent (if the child is aged ≥8), and either verbal or documented evidence of having received PCV13. Among adults, inclusion criteria include: aged 18–40 years, providing written informed consent, and being HIV-infected and receiving ART.

Among children 9 months of age, recruited as part of the safety component, inclusion criteria include: aged 9 months, parent/legal guardian providing written informed consent, and evidence (recorded in health passport) of having received either a full 3+0 PCV13 vaccine schedule (health centres implementing 3+0) or both primary doses of PCV13 at approximately 6 and 14 weeks of age (health centres implementing 2+1).

Exclusion criteria for all screened individuals include receiving TB treatment at time of screening, hospitalisation for pneumonia within 14 days prior to study screening and terminal illness. Exclusion criteria for all children include parental/legal guardian not providing consent, not providing assent (for children aged ≥8 years), having received antibiotic treatment within 14 days prior to study screening. Exclusion criteria for adults include not providing written informed consent or prior vaccination with a pneumococcal vaccine.

### Intervention

The intervention will consist of two carriage surveys conducted 18 and 33 months after the 10 randomised health centres switch from a 3+0 to a 2+1 PCV13 schedule. In both surveys, a single NP swab will be collected from each participant. Following previously described WHO-recommended procedures,^45 49^ these will be collected and taken to the Malawi-Liverpool-Wellcome Trust Clinical Research Programme laboratory in Blantyre for the isolation and characterisation of *S. pneumoniae*. VT pneumococcal carriage will be serotyped by latex agglutination. Samples from participants with confirmed pneumococcal carriage will be sent to the UK for assessment of multiple serotype carriage (genomic microarray) and for whole genome sequencing.

### Expected outcomes

The primary endpoint of this study will be the difference in VT pneumococcal carriage prevalence among children aged 15–24 months, comparing those vaccinated with PCV13 in either a 2+1 or 3+0 schedule, 3 years after implementing the switch to a 2+1 schedule. Additionally, the study will evaluate four secondary outcomes: (1) difference in VT carriage prevalence among children 5–10 years old, 18 months and 33 months after 2+1 implementation, (2) VT carriage prevalence among HIV-infected adults aged 18–40 years and receiving ART at the time of sampling, (3) VT carriage prevalence among infants aged 9 months, who will have received three primary doses (3+0 health centres) or two primary doses (2+1 health centres) prior to the booster dose, 9 months after the implementation of the 2+1 schedule and (4) prevalence of multiple serotype carriage, 18 and 33 months after 2+1 implementation

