### Statistical analyses

Continuous variables will be summarised by means and SD, or medians and IQRs if the distribution exhibits skew. Categorical variables will be summarised by frequency distributions. Direct effects of the PCV13 schedule change on VT carriage will be ascertained by comparing carriage prevalence in children aged 15–24 months residing in the recruitment clusters of health centres randomised to the 2+1 schedule and those in recruitment clusters of health centres randomised to the 3+0 schedule. Indirect effects will be evidenced by comparing children in the recruitment clusters of health centres randomised to the 3+0 schedule among older children (5–10 years) and HIV +adults. Additionally, data obtained in this study will be compared with those obtained from previous carriage surveys to ascertain any changes in VT carriage prevalence before and after the PVC13 schedule change. Statistical tests will be selected depending on the distribution patterns of the data. Potential confounders and sources of interaction (including age, gender and health centre) will be identified by testing the association between variables and VT carriage and included in the multivariable models when p<0.1. Sensitivity analyses will include assessing impact of (1) receiving only one, only two or all three doses PCV; (2) having document-confirmed PCV vaccination or (3) schedule adherence to within 2 weeks of each scheduled dose on VT prevalence and on the VT distribution.

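### The primary contrast is worded by schedule received in one section and by randomised cluster in another, and the full-schedule entry rule selects the two arms at different visits

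*Protocol article*

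**What the plan says.** Expected outcomes defines the primary endpoint as a difference in vaccine-type (VT) carriage at 15–24 months, "comparing those vaccinated with PCV13 in either a 2+1 or 3+0 schedule". Read literally, that groups children by the schedule they had.

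Statistical analyses obtains the direct effect by comparing "children aged 15–24 months residing in the recruitment clusters of health centres randomised to the 2+1 schedule" with the corresponding residents of 3+0 clusters. That groups them by allocation.

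Inclusion and exclusion criteria admits children in this age group only with "evidence (recorded in health passport) of having received a full schedule of PCV13". Study questions defines the schedules: 2+1 is "two primary doses at 6 and 14 weeks of age +1 booster dose at 9 months of age", and 3+0 is "three primary doses at 6, 10 and 14 weeks of age with no booster".

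The Carriage surveys section accepts that a child's schedule may differ from the cluster's. It describes contamination as "recruitment of children receiving a PCV13 vaccine schedule different than the schedule assigned" to the local health centre, and uses inner and outer sampling perimeters to limit it. The Introduction describes the 2+1 option as "providing a booster dose at the time of the first measles vaccine at 9 months of age".

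**The concern.** There are two separate issues.

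The first is grouping. A child living in a 2+1 catchment with a complete 3+0 record counts as 2+1 under one section and as 3+0 under the other. No section says which governs. Grouping by schedule received would let moving house or choosing another clinic decide a child's arm, and neither is randomised.

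The second is selection. Whichever grouping is used, the entry rule acts after randomisation and depends on different visits in the two arms. Children who drop out of routine care between 14 weeks and 9 months are kept under 3+0 and lost under 2+1. If they also carry more VT, the 2+1 arm looks better with no schedule effect at all. The planned sensitivity analysis by one, two or three doses cannot show this in the main sample, because children short of a full schedule are not enrolled.

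**Working it through.** **The plan's own figure.** Inputs from Study power and sample size calculation: 14% v 7%, 80% power, alpha 0.05 (taken as two-sided), ICC 0.005, 40 per cluster. With mean proportion 0.105:

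n = [1.960·√(2·0.105·0.895) + 0.842·√(0.14·0.86 + 0.07·0.93)]² / 0.07² = 300 per arm.

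Design effect = 1 + 39·0.005 = 1.195, and 300·1.195 = 358.5, against the stated 358. The planned 400 per arm gives about 84% power. The sample size reproduces and is not in question, but no allowance for crossover is stated.

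**What the grouping changes.** The article gives no crossover rate. Assume a fraction x of each arm's children had the other schedule, and that carriage follows the schedule received.

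- 3+0 clusters at x = 10%: 0.14·0.9 + 0.07·0.1 = 13.3%.
- 2+1 clusters at x = 10%: 0.07·0.9 + 0.14·0.1 = 7.7%.
- By randomised cluster: 5.6 points, a 42% reduction. By schedule received: 7.0 points, 50%.
- Power by randomised cluster (400 per arm, design effect 1.195): 84% at x = 0, 76% at 5%, 66% at 10%.

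The as-received figure is unbiased only if crossover is unrelated to a child's carriage risk.

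**What the entry rule does.** Suppose there is no schedule effect, with 14% carriage in both arms before filtering. Let f be the fraction removed from the 2+1 arm for want of the booster, g the fraction removed from the 3+0 arm, and r the carriage of removed children relative to those kept. Prevalence among those kept is 0.14/[(1−f) + f·r] in 2+1, and likewise with g in 3+0. The spurious ratio (2+1 over 3+0) is therefore [(1−g) + g·r] / [(1−f) + f·r]. All three inputs are assumptions.

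| f | r | Spurious reduction, g = 0 | Spurious reduction, g = 5% |
|---|---|---|---|
| 10% | 1.2 | 1 − 1/1.02 = 2.0% | 1 − 1.01/1.02 = 1.0% |
| 10% | 1.5 | 1 − 1/1.05 = 4.8% | 1 − 1.025/1.05 = 2.4% |
| 20% | 1.2 | 1 − 1/1.04 = 3.8% | 1 − 1.01/1.04 = 2.9% |
| 20% | 1.5 | 1 − 1/1.10 = 9.1% | 1 − 1.025/1.10 = 6.8% |

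With g = 0 the bias is 0.3 to 1.3 percentage points on 14%. The standard error of the difference at 14% in both arms is √(2·0.14·0.86·1.195/400) = 2.7 points, so the bias is at most about half a standard error. It vanishes when g = f, and reverses if r is below 1 or if g exceeds f (with r above 1).

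**The case against.** The strongest reply is that the analysis section already names the randomised cluster, and that the endpoint sentence merely describes who is sampled. Other text agrees: the inclusion criteria speak of children assigned to a schedule, the sample size section speaks of arms, and contamination is defined against the health centre's assigned schedule. Nothing says a crossover child is moved to the other arm. This stands. A reader might infer that the randomised comparison has been abandoned; the article does not support that. What remains is an endpoint sentence that, taken literally, says something else.

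A reader might also infer that the entry rule filters the 2+1 arm alone. It does not. Both schedules have three doses: the 10-week dose is required only under 3+0 and the 9-month dose only under 2+1, so both arms lose children. Nor does missing the 9-month visit remove a child automatically. No timing limit is set for this age group, and the planned sensitivity analysis on adherence to dose dates implies that late doses are accepted.

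Restricting to vaccinees is also deliberate, since the primary objective is a direct effect. That justifies a restriction, but not one that depends on different attendance in each arm. Finally, analysis-set detail may sit in a statistical analysis plan that is not shown. That answers a charge of omission, but not two differing statements within the article or an entry rule fixed at recruitment.

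**Conclusion.** The point holds in a limited form. The endpoint wording and the analysis wording differ and should be aligned on the randomised cluster. The full-schedule rule selects the arms on different post-randomisation attendance, and the planned sensitivity analyses cannot recover the children it excludes.

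The likely bias is modest: at most a 2–9% relative reduction under the assumed 10–20% missed and 1.2–1.5 times the carriage, and 1–7% if 5% are also excluded under 3+0. That compares with a 50% target. Even the direction depends on non-attenders carrying more VT and on more children being lost under 2+1 than under 3+0. The article gives no rate for any of these. The crossover figures (42% v 50%) show how far the two groupings could diverge under an assumed 10%; they do not measure an error in the plan.

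**What to change.** - **Grouping.** Reword the endpoint in Expected outcomes to match Statistical analyses: children are grouped by the randomised allocation of the health-centre cluster they live in, whatever schedule the passport shows. Make as-received grouping a sensitivity analysis.
- **Entry rule.** Apply a common attendance condition by also requiring a recorded 9-month (first measles vaccine) visit in the 3+0 arm, with the same latitude for lateness in both arms. Failing that, pre-specify this restriction as a named sensitivity analysis, accepting that the primary comparison then keeps the imbalance.
- **Reporting.** Report, by arm, the number screened out for an incomplete schedule and which dose was missing. This also shows the size of the 10-week exclusions, which the 9-month condition leaves untouched.

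The cost is small: some wording, slightly fewer eligible 3+0 children, and one more passport item to record. Passports are already reviewed for PCV13, but the article does not say that measles-vaccine dates are captured. The as-randomised effect may be somewhat smaller than the as-received one, with lower power if crossover is appreciable.
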